### Measurements

#### Primary outcome measures (for patients)

*Eating Disorder Examination Questionnaire* (EDE-Q) [31, 32]. The EDE-Q is derived from the Eating Disorder Examination Interview (EDE) (Fairburn & Cooper, 1993) and is commonly used to assess the frequency of core ED behaviors and the attitudinal features related to ED pathology over the past 28 days. Twenty-two of the 36 items assess attitudes related to ED pathology and are divided into four subscales (concerns about weight, shape and eating, and restraint). Items are rated on a 7-point Likert scale ranging from 0 = not 1 day/not at all, to 6 = every day/markedly. The core ED behaviors (remaining 14 items) are assessed in terms of their presence and frequency. A global score of eating psychopathology can be calculated by summing and averaging all of the items. Higher scores indicate higher ED psychopathology. The EDE-Q has demonstrated good reliability and validity both in its original version [33] and in Spanish [32].

*The Short Evaluation of Eating Disorders* (SEED) [8, 34]. The SEED was developed for the assessment of key ED symptoms. It includes 3 items related to AN symptoms (degree of underweight, fear of weigh gain and distortion of body perception) and 3 items related to BN symptoms (amount of binge eating episodes, amount of compensatory behaviors and over concern with body shape and weight). The questionnaire allows the calculation of two severity indices for AN and BN (range from 0 to 3). The construct validity and the criterion-related validity of the SEED yielded positive results and the sensitivity to change of the instrument was also satisfactory [34].

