### Sample size calculation

The a priori sample size calculation was based on results from previous studies that implemented Internet-based programs in the treatment of EDs [58–60]. A small between-group effect size (Cohen’ s d = 0.40) is expected. The calculation was conducted by the software program G*POWER. The primary analysis will concern the hypothesis that the average level of eating pathology at post-intervention in the control group, based on the EDE-Q scores, will be higher than the average levels of eating pathology in the experimental group. Assuming an alpha of 0.05 and a power of 0.80 (β − 1) in an independent samples one-way t-test study, a minimum of 100 participants would be required per study arm. Allowing for a dropout rate of 25% of study participants from baseline, a total of 250 participants need to be recruited.

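### The protocol's only EDE-Q scoring rule averages attitude ratings (0 to 6) with 14 presence-and-frequency items, so this primary measure has no defined scale

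*Protocol article*

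**What the plan says.** The EDE-Q is the first of two instruments under Primary outcome measures (for patients); the other is the SEED. The EDE-Q paragraph makes four statements in this order:

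- The split of items: "Twenty-two of the 36 items assess attitudes related to ED pathology and are divided into four subscales".
- The rating scale: "Items are rated on a 7-point Likert scale ranging from 0 = not 1 day/not at all, to 6 = every day/markedly".
- The other items: "The core ED behaviors (remaining 14 items) are assessed in terms of their presence and frequency".
- The overall score: "A global score of eating psychopathology can be calculated by summing and averaging all of the items".

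The recall period is 28 days. No coding is given for the 14 behaviour items, and no range for the global score.

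The Sample size calculation section states the primary hypothesis as a comparison of average eating pathology after the intervention, where the control level, "based on the EDE-Q scores, will be higher than the average levels of eating pathology in the experimental group". It does not say whether these scores are the global score, a subscale or a behaviour frequency.

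**The concern.** The scoring rule comes directly after the sentence that sets the 14 behaviour items apart, and nothing limits it to the 22 attitude items. As written, it adds ratings on a 0 to 6 scale to answers recording whether, and how often, a behaviour occurred. Such a sum has no unit, and its size depends on how the behaviour answers are coded.

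This matters because the EDE-Q carries the primary hypothesis, and the global score is the only overall EDE-Q score that the article describes. Two analysts could follow the article faithfully and derive different primary variables from the same data. The Economic evaluation section also takes effects on the EDE-Q into account, so the ambiguity carries over to it.

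Eligibility is broad: anorexia nervosa, bulimia nervosa, binge eating disorder, purging disorder, night eating syndrome and related presentations. Patients can therefore be expected to differ in how many of the listed behaviours they report. Under the literal rule, that difference moves the score even when their attitudes are equally severe.

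**Working it through.** **The plan's own figure.** Inputs from the Sample size calculation section: "d = 0.40) is expected" and "Assuming an alpha of 0.05 and a power of 0.80"; allocation is 1:1 (Design section). A two-sided independent-samples t-test needs 99.08 per arm, so 100, which reproduces the stated minimum. The effect is given in standard deviation units, with no raw EDE-Q difference or SD. The EDE-Q scoring rule therefore does not enter this calculation, and the 100 per arm stays as it is.

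**Inputs for the score.** All from the EDE-Q paragraph: 22 attitude items rated 0 to 6, 14 behaviour items with coding not stated, and a global score equal to the sum of all 36 items divided by 36. The behaviour items are 14/36 = 39% of the items.

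**Range of the score**

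| Items averaged | Coding of the 14 items | Maximum |
|---|---|---|
| 22 attitude items | not used | 6 |
| All 36 | 0/1 (assumption) | (22 × 6 + 14 × 1)/36 = 146/36 = 4.06 |
| All 36 | 0 to 28 days each (assumption, from the 28-day recall) | (22 × 6 + 14 × 28)/36 = 524/36 = 14.56 |

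The two codings only show the spread. The article supports neither over the other.

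**Equal attitudes, different scores.** Take a patient whose attitude items average 4.0, a sum of 22 × 4.0 = 88. The behaviour averages below are assumptions.

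| Average of the 14 behaviour items | Score under the literal rule |
|---|---|
| 0 | 88/36 = 2.44 |
| 1 | (88 + 14)/36 = 2.83 |
| 4 | (88 + 56)/36 = 4.00 |
| 14 | (88 + 196)/36 = 7.89 |

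With no behaviours, the score is 22/36 = 61% of the attitude mean, or 39% lower. It equals the attitude mean only when the behaviour items happen to average the same value.

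**Share of the score due to behaviours.** With attitude items averaging 3 (assumption; sum 66), the behaviour items supply 14/(66 + 14) = 17.5% of the total at an average of 1, 56/(66 + 56) = 46% at 4, and 196/(66 + 196) = 75% at 14.

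**The case against.** The best defence is that the sentence is loose shorthand. It stands in an instrument description, says only that a score can be calculated, and refers to a cited, validated questionnaire. The analysts may well intend to score it coherently. It could also be argued that the rating-scale sentence covers all 36 items, so that no units are mixed. The first argument may explain the wording, but it does not correct it: the article contains no other rule. The second does not fit the text, because the next sentence describes the remaining 14 items differently, by presence and frequency.

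Three stronger readings are tempting, and the article does not support them.

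- **That the global score is the declared primary endpoint.** It is not declared. The sample size section refers only to EDE-Q scores. The global score is the natural reading, because it is the only overall score described.
- **That the score departs from a scale promised by the plan.** The 0 to 6 range is stated for item ratings. No range is given for the global score.
- **That the composite dilutes the effect and costs power.** This depends entirely on assumptions. Suppose an attitude-mean SD of 1.3, five independent count items with SD 6, a d of 0.40 on attitudes and no effect on behaviours. The sum then has SD √(28.6² + 5 × 6²) = 31.6, and d falls to 11.44/31.6 = 0.36. But d = 0.40 needs a summed difference of 12.64. The missing 1.20 is 0.24 per count item, or 0.04 SD. With SD 12 per item, the required effect is 0.07 SD. At 0.10 SD per item, the composite d is about 0.46 (SD 6) or 0.44 (SD 12), above 0.40. The trial expects improvement in eating disorder symptoms, and the SEED, its other primary measure, includes binge episodes and compensatory behaviours. An assumption of no effect on behaviours is therefore hard to defend.

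Nor does the 39% figure show lost power. Among patients with no behaviours, it is a constant rescaling and leaves a standardised difference unchanged. It bears on interpretation and on comparison across diagnoses.

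**Conclusion.** The point holds as an internal inconsistency in the definition of a primary outcome measure. The article separates two kinds of item and then instructs that all of them be averaged. On that rule, the score's maximum could be anywhere from 4.06 to 14.56 under the two illustrative codings, against 6 for the attitude items alone. Patients with the same attitude severity would receive different scores depending on their behaviours. The only facts needed from the article are the 22/14 split, the 0 to 6 ratings and the wording of the rule; the codings and behaviour averages are assumptions used to show the spread.

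The consequence is an undefined scale and avoidable discretion in scoring the primary variable. Sample size, design and data collection are not affected, and no conclusion is drawn about power or effect size.

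**What to change.** Before analysis, replace the scoring sentence with one stating that the primary EDE-Q variable is the global score computed from the 22 attitude items only, on a 0 to 6 scale. Use the same name for it in the primary hypothesis of the sample size section. Analyse the 14 behaviour items separately, as secondary presence or frequency outcomes, with their coding stated.

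The sentence should also say how the 22 items are combined. A mean of the 22 items and a mean of the four subscale scores generally differ when subscales have unequal numbers of items, and 22 does not divide evenly by four. The article gives no subscale scoring rule, so the sponsor should name the one used.

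The cost is one or two sentences. All items are already collected, and the sample size does not change.

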#### Secondary outcome measures

##### For patients

*Beck Depression Inventory* (BDI-II) [35]. The BDI-II is an instrument used for assessing the severity of depression in adult and adolescent patients over a period of 2 weeks. It includes 21 items, which are answered on a 4-point Likert scale ranging from 0 (not at all) to 3 (extreme form of each symptom). The total score is obtained by summing the severity ratings of each depression item. The questionnaire showed strong internal consistency and good test-retest reliability in both English and Spanish languages, among clinical and non-clinical samples [36, 37].

*State-Trait Anxiety Inventory* (STAI) [38]. The STAI is composed of 20 items for assessing trait anxiety and 20 items for state anxiety. Responses are on a 4-point Likert scale, ranging from “Almost never” to “Almost always”. Higher scores indicate higher levels of anxiety. The instrument showed satisfactory reliability with Cronbach’s α ranging from 0.86 to 0.95 and also test-retest reliability coefficients ranged from 0.65 to 0.75 over a 2-month interval [38]. The Spanish validation by Spielberger, Gorshuch and Lushene [39] showed satisfactory reliability for State Anxiety (0.90-0.93) and for Trait Anxiety (0.84-0.87). Test-retest reliability varied 0.73 and 0.86 on STAI-T [40].

*Anorexia Nervosa Stages of Change Questionnaire* (ANSOCQ) [41] and the *Bulimia Nervosa Stages of Change Questionnaire* [42] will be used to measure patients’ readiness to recover behaviours and attitudes related to their eating disorder. In particular, the ANSOCQ is used for AN patients and the BNSOCQ for patients with BN or Binge Eating Disorder. Both questionnaires are composed of 20 items and scores on each item range from 1 to 5, following stages of change model by Prochaska and colleagues (1998) [43], according to which "1" signifies the Precontemplation stage, "2" is for Contemplation, "3" is for Preparation, "4" is for Action and "5" is for Maintenance. Total scores are obtained by summing the individual items and range from 20 to 100. The ANSOCQ showed good internal consistency and one-week test-retest reliability, both in the English and Spanish version [44]. In turn, the validation study of the BNSOCQ, which was conducted in Spain, demonstrated good internal consistency with Cronbach’s alpha of 0.94 and one-week test-retest reliability of 0.93 [42].

*Beck Hopelessness Scale* (BHS) [45]. The BHS is a 20-item questionnaire designed to measure negative attitudes about the future in clinical and research settings. More specifically, it measures three major aspects of hopelessness: feelings about the future, loss of motivation and expectations. The Spanish validation of the instrument showed adequate reliability (Cronbach’s α ranging from 0.82 to 0.84) and moderate construct validity [46].

*EQ-5D-5 L* and *EQ-5D-Y* [47]. The EuroQoL-EQ-5 L is a standardized instrument used as a health outcome measure for economic evaluation studies. It consists of five dimensions: mobility, self-care, usual activities, pain/discomfort and anxiety/depression. Each dimension has 5 levels: no problems, slight problems, moderate problems, severe problems and extreme problems. The questionnaire also includes an EQ Visual Analogue scale (EQ VAS) about how good or bad the individual’s health is today. The EQ-5D-5 L has been validated in 6 countries, including different groups of patients with chronic conditions and a student cohort. The psychometric properties of EQ-5D-5 L were superior to the previous version of the instrument (EQ-5D-3 L) in terms of validity, although reliability remains to be assessed for the EQ-5D-5 L. In addition, the child-friendly EQ-5D version (EQ-5D-Y) [48] will be used for children and adolescents following and same structure as the EQ-5D (descriptive system and EQ VAS).

*iMTA questionnaire for Costs associated with Psychiatric Illness* (TiC-P) [49]. The TiC-P will be used for adult patients only, to evaluate the healthcare utilization due to the psychiatric illness, such as number of patient visits to their general practitioner, medical specialists and paramedics, during the last 3 months. The questionnaire will also assess productivity losses due to absence from work or due to reduced efficiency during paid or unpaid work, as well as medication consumed due to the patient’s psychiatric disorder. The instrument establishes direct medical costs and productivity costs and is widely used among different countries for economic evaluations in mental health. The Spanish version of the questionnaire has been obtained upon permission from the original authors. The feasibility and reliability of the instrument was satisfactory and the construct validity of the questions related to healthcare utilisation and long-term work absenteeism was also good [50].

The *System Usability Scale* (SUS) [51, 52]. The SUS is a 10-item questionnaire with five response options that range from 4 = “Strongly agree” to 0 = “Strongly disagree”. The SUS provides a “quick and dirty” reliable tool for measuring the usability of a range of systems. The participant’s scores for each question are converted to a new number, added together and then multiplied by 2.5 to convert the original scores of 0-40 to 0-100.

*Client Satisfaction Scale* (CSQ-8) [53]. The CSQ-8 is an 8-item questionnaire that is designed to measure client satisfaction with services. Scores are on a 4-point Likert scale and range from 8 to 32, with higher scores indicating greater satisfaction. The instrument showed satisfactory reliability with Cronbach’s α ranging from 0.83 to 0.93 and correlations of the instrument with other measures of general satisfaction ranged from 0.6 to 0.8. The CSQ-8 is also available in Spanish by Martínez and Beiti [54].

##### For clinicians responsible for the online monitoring

*Suicide Intent Scale* (SIS) [55]. The SIS is a questionnaire that measures the severity of the suicide attempt and should be fulfilled by the clinician responsible for the treatment of the patient. The scale consists of 20 questions, which are scaled from 0 to 2 and cover three aspects: 1) objective circumstances surrounding the attempt, 2) perceptions of potential lethality, expectations of rescue, purpose of the attempt, impulsivity and reaction to the attempt and 3) other aspects. Both the English and the Spanish version of the instrument showed satisfactory reliability and validity [55, 56].

The *System Usability Scale* (SUS) [51, 52].

*Client Satisfaction Scale* (CSQ-8) [53].

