The purpose of this trial is to conduct a multicentre, randomized controlled trial with 250 patients diagnosed with an ED. In this experiment, the patients from the experimental group will test a mHealth application (TCApp developed by HealthApp) and then, a clinical efficacy analysis and economic evaluations will be performed. To do this, we have set the following three specific objectives:To evaluate the clinical efficacy of an intensive intervention that includes both standard face-to-face Cognitive Behavioural Treatment (CBT) (treatment as usual, TAU) plus mHealth intervention using the TCApp, versus the TAU alone.To carry out an economic evaluation of the new mHealth intervention and identify factors that promote or hinder the implementation of the TCApp in mental health settings in Spain.To analyse the adoption processes of this type of applications by patients and health professionals and identify the determinants of mHealth adoption.

The implementation of the intensive intervention program (TAU + TCApp) would result in a more significant improvement of the ED symptoms compared to the TAU control group. More specifically:The application of the intensive mHealth intervention would lead to significantly greater change scores (difference between T0 and T1, which will be also maintained at follow-up, T2) in the primary outcome variable of ED psychopathology, compared to the control group.The mHealth intervention would lead to significantly greater change scores (difference between T0 and T1, which will be also maintained at follow-up, T2) in patients’ secondary outcome variables: a) depression symptoms, b) anxiety symptoms, c) readiness to recover, d) suicidal risk, and e) quality of life, compared to the control group.Similarly, intensive intervention would result in greater change scores (difference between T0 and T1, which will be also maintained at follow-up, T2) in caregivers’ variables: a) quality of life and b) caregiver burden.

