**Fig. 1 Fig1:**
[figure not shown]
Timeline and procedure

**Table 1 Tab1:** Instruments for measuring clinical efficacy and cost-effectiveness

Dimension	Methodology	Assessment measures	Stakeholder	T0	T1	T2
Clinical efficacy						
Psychopathology	Clinical interview	**Minors** (6-18 years old): Kiddie Schedule for Affective Disorders and Schizophrenia-Present and Lifetime version (K-SADS-PL) (DSM-5) **Adults**: Structured Clinical Interview for DSM Disorders (SCID-I)	Patient	x		
Physical and clinical variables	Brief clinical interview	Comorbidities, medication, illness duration, Body Mass Index, among others	Patient	x	x	x
Eating Disorder psychopathology	Questionnaire	- Eating Disorders Examination Questionnaire (EDE-Q) - Short Evaluation of Eating Disorders (SEED)	Patient	x	x	x
Depression	Questionnaire	Beck Depression Inventory-II (BDI-II)	Patient	x	x	x
Anxiety	Questionnaire	State-Trait Anxiety Inventory (STAI)	Patient	x	x	x
Motivation to change	Questionnaire	**Patients with Anorexia Nervosa**: Anorexia Nervosa Stages of Change Questionnaire (ANSOCQ) **Patients with Bulimia Nervosa or Binge Eating Disorder**: Bulimia Nervosa Stages of Change Questionnaire (BNSOCQ)	Patient	x	x	x
Dropout	Telephone interview	Reasons for dropout	Clinician responsible for the online monitoring		x	x
Risk of suicide	Questionnaire	Beck Hopelessness Scale (BHS) / Suicide Intent Scale (SIS)	Patient / Clinician responsible for the online monitoring	x	x	x
Quality of life	Questionnaire	**12-14 years old**: EQ-5D-Y (children version) **> 14 years old**: EQ-5D-5 L	Patient	x	x	x
Caregiving experience	Questionnaire	Experience of Caregiving Inventory (ECI)	Family caregiver	x	x	x
Quality of life	Questionnaire	EQ-5D-5 L	Family caregiver	x	x	x
Cost-utility and cost-effectiveness analysis						
Cost related to the development and maintenance of the online platform	Telephone interview	Staff involved, number of extra hours x pay rate/hour	Technical staff	x	x	
Costs related to healthcare utilization, medication and school and / or work absenteeism	Questionnaire	iMTA questionnaire for Costs associated with Psychiatric Illness (TiC-P) / iMTA questionnaire for Costs associated with Psychiatric Illness, Parent-Form (TiC-P Children)	Adult patient / family caregiver (referring to minor patient)	x	x	x

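### The Suicide Intent Scale rates an actual attempt, so its scheduled T0–T1–T2 scores cannot supply a change score for patients without one; the hopelessness scale can, and the SIS rater needs reconciling

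*Protocol article*

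**What the plan says.** All references are to the protocol article.

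- **What the SIS is.** Under Secondary outcome measures, in the part headed "For clinicians responsible for the online monitoring", the scale is said to be one that "measures the severity of the suicide attempt and should be fulfilled by the clinician responsible for the treatment of the patient". The first group of items covers "objective circumstances surrounding the attempt". The second group covers matters such as expected rescue, purpose and reaction, again in relation to an attempt.
- **When and by whom.** The risk-of-suicide row of Table 1 holds the BHS and the SIS together, with marks at T0, T1 and T2. It gives the respondents as "Patient / Clinician responsible for the online monitoring".
- **What is to be shown.** The hypotheses at the end of the Background state: "The mHealth intervention would lead to significantly greater change scores (difference between T0 and T1", with the difference kept at T2. The list of patients' "secondary outcome variables: a) depression symptoms, b) anxiety symptoms, c) readiness to recover, d) suicidal risk" then ends with quality of life.
- **How it is to be analysed.** The Statistical analysis section applies a linear mixed model, with terms for visit, arm and their interaction, to the primary and secondary measures.
- **Who is enrolled.** The Inclusion and Exclusion criteria admit day-hospital and outpatient cases of any severity and duration. No criterion concerns a past or recent suicide attempt.
- **The other instrument.** Under the measures for patients: "The BHS is a 20-item questionnaire designed to measure negative attitudes about the future in clinical and research settings".

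**The concern.** A scale that grades the severity of an event has a value only where the event took place. The plan uses such a scale as if it were a continuous state that every patient has at every visit, and attaches a change-score hypothesis and a longitudinal model to the outcome it serves. Taken as written, clinicians would be asked three times to grade an attempt for patients who may never have made one. The analyst would then have to improvise a rule for the empty cells, and the two obvious rules both damage the randomised comparison.

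A second, smaller problem concerns the rater. The sentence describing the SIS gives the task to the clinician in charge of treatment. Its own heading and Table 1 give it to the clinician in charge of online monitoring. Study conditions assigns monitoring to nurses at most centres, so these need not be the same person.

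**Working it through.** The plan gives no figure for the SIS that could be reproduced, so the check is mainly a comparison of statements, followed by a range calculation.

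**Step 1: is a change score defined?** Write S(t) for a patient's SIS score at visit t. The hypothesis needs S(T1) − S(T0), and then the same contrast at T2. By the article's description, S(t) exists only if there is an attempt to grade at t.

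| Patient | S(T0) | S(T1) | Change |
|---|---|---|---|
| No attempt at any time | none | none | undefined |
| Attempt only before T0 | exists | none, or the same event graded again | undefined, or re-grading of one event |
| Attempt only between T0 and T1 | none | exists | undefined |
| Separate attempts ratable at T0 and at T1 | exists | exists | defined, but compares two different events |

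The BHS asks about attitudes to the future and needs no attempt, so its change score is defined for everyone who completes it at both visits.

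**Step 2: does the mixed model repair this?** A mixed model can use patients with incomplete series, but it treats an absent score as a value that exists and was not observed. For a patient without an attempt there is no such value. The T1 and T2 means would be estimated from patients who had something to grade.

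**Step 3: the two obvious rules for patients without an attempt.**

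- *Analyse only those with an attempt after T0.* This selects on an event after randomisation that the intervention may affect, so the arms compared are no longer the randomised arms.
- *Score the others 0.* If a share p of an arm has an attempt and the mean severity among them is s, the arm mean is p × s. Occurrence and severity can no longer be separated. An arm with p = 10% and severity s has mean 0.10 × s. An arm with p = 20% and severity s/2 has mean 0.20 × s/2 = 0.10 × s, which is identical although twice as many patients made an attempt.

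**Step 4: how many patients could have a score?** Inputs: N = 250 (Sample; Sample size calculation), 1:1 allocation (Design), and p, the share with an attempt to rate. The documents do not give p, so it is varied as an assumption. Patients with any SIS score = 250 × p; per arm = 250 × p / 2.

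| p (assumed) | Any SIS score, of 250 | Per arm | No SIS score |
|---|---|---|---|
| 2% | 5 | 2.5 | 245 |
| 5% | 12.5 | 6.25 | 237.5 |
| 10% | 25 | 12.5 | 225 |
| 20% | 50 | 25 | 200 |
| 30% | 75 | 37.5 | 175 |
| 50% | 125 | 62.5 | 125 |

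A change score needs a ratable attempt at both visits, so the second and third columns are upper bounds for it.

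**Step 5: the rater.** Three statements apply to the same scale. The heading of the subsection names the monitoring clinician, the sentence beneath it names the treating clinician, and Table 1 names the monitoring clinician. Two agree and one differs.

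**The case against.** The strongest reply is that the suicidal-risk hypothesis does not depend on the SIS. The Background does not name the scale, and the BHS sits in the same row of Table 1. That stands. A reader might infer that the suicidal-risk outcome as a whole cannot be tested, but the documents do not support this: every BHS respondent has a score at each visit.

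A second reply is that the slash in Table 1 may mean that the SIS is completed only where it applies, as the adult and parent forms of the cost questionnaire are separated by a slash. Scoring and applicability rules for one secondary scale may also sit in the full protocol or analysis plan. This is fair as far as the missing rule goes. It does not remove the mismatch. The article itself states an attempt-severity scale, three scheduled visits, a change hypothesis and a longitudinal model, and no later rule can grade an attempt that did not occur. Completing the scale only where applicable leads back to the selection problem in Step 3.

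Three further inferences go too far:

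- *Most patients lack a score.* This is true for any p below 50% and is plausible in a sample not selected for attempts. It still rests on a rate that the documents do not give.
- *The text conflicts with Table 1 on the rater.* The subsection heading agrees with the table. Only one sentence differs, and it could be a general description of the instrument.
- *Attempts will be detected more often in the app arm.* Background says the app can raise alarms on certain words, and Study conditions has the monitoring clinician follow daily records. The article does not say who receives the alarms, nor that the SIS is used to detect attempts. Unequal detection is a possibility to note and is not shown.

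**Conclusion.** The point holds for the SIS component only. By the article's own description, the SIS has no defined change score for a patient without a ratable attempt at both visits, so it gives no valid between-arm change estimate under the stated hypothesis and model. The BHS component is sound. The size cannot be computed from the documents; the table in Step 4 is a range over assumed rates. The rater inconsistency is real and lies in one sentence set against its own heading and Table 1.

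Severity is minor. One of two instruments for one secondary outcome is affected, and the primary analysis on the EDE-Q is untouched.

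**What to change.** 1. State that the BHS alone carries the change-score hypothesis for suicidal risk. It measures hopelessness, and the text should say so.
2. Report, per arm, the number of patients with at least one attempt in T0–T1 and in T1–T2. Give SIS scores descriptively for those patients only, without a between-arm test. Add a note that clinicians in the app arm may have more information about their patients, so the counts should be read with that in mind.
3. Reconcile the sentence naming the treating clinician with its heading and Table 1, so that the same type of clinician completes the SIS in both arms.

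The cost is protocol wording, with no new instrument or visit. The downside is one fewer scale in the between-arm tests.
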